##### Classification of the predictors

We have chosen collectively to classify as ‘standard predictors’ the below mentioned groups of predictors, i.e. (1) clinical predictors, (2) current medical treatment, and (3) standard biochemical predictors. The term ‘standard predictors’ is only a collective term used by us in this particular study to refer to those baseline quantities that were available to us during the CLARICOR trial and which are either established prognostic predictors or proxies of such predictors not available to us [31, 32]. The biochemical predictors we have measured in addition for the present PREMAC study are labelled ‘advanced biochemical predictors’. The two groups of predictors, i.e. ‘standard predictors’ and ‘advanced biochemical predictors’ are defined below.I.Standard predictorsClinical predictorsSex, age, smoking history, history of myocardial infarction compared to angina only, hypertension, and diabetes.Current medical treatmentAspirin (Yes/No), beta-blocker (Yes/No), calcium-antagonist (Yes/No), ACE-inhibitor (Yes/No), long lasting nitrate (Yes/No), diuretic (Yes/No), digoxin (Yes/No), statin (Yes/No), and anti-arrhythmic drugs (Yes/No). The current medical treatment was included as proxy predictors because information about post-infarction heart failure and post-infarction angina pectoris are not available to us.Standard biochemical predictorsHigh-sensitivity-reactive protein, glomerular filtration rate (GFR) estimated by creatinine, and lipoproteins (total cholesterol, HDL cholesterol, LDL cholesterol, triglycerides, apoprotein A1, and apoprotein B).
II.Advanced biochemical predictorsN-terminal pro-B-type natriuretic peptide, YKL-40, osteoprotegerin, hs-cTnT, PAPP-A, cathepsin B, cathepsin S, sTNFR1, sTNFR2, NGAL, endostatin, and calprotectin. Tests for all these quantities are commercially available.

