#### The patients

The patient group is defined by the inclusion and the exclusion criteria of the patients who, during the winter 1999–2000, entered the CLARICOR trial.

The CLARICOR trial was an investigator-initiated, randomised, placebo-controlled, multicentre superiority trial including outpatients with stable coronary artery disease (CAD), using central 1:1 randomisation and blinding of all parties. All patients discharged from wards or outpatient clinics in the Copenhagen area were available in an existing database. We invited all 13,702 patients who were alive and aged 18–85 years in 1999 and identified with a diagnosis of myocardial infarction or unstable angina pectoris during the years 1993–1999 to visit one of five cardiology centres in the Copenhagen area. Six thousand one hundred sixteen (44.6%) patients accepted the invitation, and of these, 4372 (71.5%) were randomised, while 1567 (25.6%) were excluded, and 177 (2.9%) refused to participate. Exclusion criteria included AMI or UAP within the previous 3 months, percutaneous transluminal coronary angioplasty and coronary bypass surgery within the previous 6 months, impaired renal or hepatic function, congestive heart failure (New York Heart Association (NYHA) IV classification of heart failure), active malignancy, incapacity to manage own affairs, breast feeding, and possible pregnancy. Between October 1999 and April 2000, the 4372 patients were randomised to receive oral clarithromycin 500 mg once daily for 2 weeks versus matching placebo to assess the effects on the risk of major cardiovascular outcomes and death.

The main results of the CLARICOR trial were that clarithromycin increased the risk of cardiovascular as well as all-cause mortality [12–14].

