##### Demographic and anamnestic data

Clinical data were obtained during enrolment interviews (smoking status, current medication, and known hypertension or diabetes), while information concerning sex, age, and history of myocardial infarction or unstable angina pectoris were obtained from the local hospital files.

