#### Flow of analyses

For each advanced biochemical quantity, we will examine if the hazard ratio of the biochemical quantity is different from 1.00 with a *P* value <0.01 when used alone and when used in combination with the standard predictors (forced to be included in the analyses whether they are significant or not). Using centre ID as a class variable, we will stratify on centre ID implying that the observations are conditionally independent within centres and that the coefficients of the covariates are the same across centres.

For each outcome, we will test for interaction between sex and each clinical predictor, each standard biochemical predictor, and each advanced biochemical predictor using Bonferroni adjusted *P* values and 0.05 as a threshold. The interactions corresponding to adjusted *P* values below 0.05 will be included in the model. Explanation will be sought for any marked discrepancies between the two settings (candidate used alone and candidate used in combination with standard predictors); but we will let us be guided by the results obtained when the latter setting is used.

Those advanced biochemical quantities which have a hazard ratio different from 1.00 and a *P* value <0.01 when used in combination with the standard predictors in the initial ‘gatekeeper’ analysis, will be included in subsequent and similar analyses of each individual outcome of the composite outcome.

We will use the *P* values of the analyses as a data-reducing device where a threshold of *P* < 0.01 is used at each decision node on our way to identify a candidate biochemical predictor among the advanced biochemical predictors. We regard the set of selected advanced biochemical predictors as the primary result of this essentially hypothesis-generating effort. However, clinically implausible results will be discussed and commented on.

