Selection bias is also a potential weakness of the study. Only 2.6% of the patients selected for the CLARICOR trial refused to participate. So far that problem seems negligible. However, among those 7586 patients who declined our invitation to visit a cardiology centre, many must have been eligible for the CLARICOR trial, and we do not know how they looked and fared. So selection bias is a possibility.

The design of the CLARICOR trial may also contribute to selection bias. In the CLARICOR trial, the rate of cardiovascular events and deaths was studied in patients who had contracted an AMI or UAP during the period January 1993 to August 1999, were alive during the randomisation period (October 1999 to April 2000) and fulfilled the inclusion criteria and none of the exclusion criteria as defined in the CLARICOR trial [10].

Normally, to assess the rates in stable CAD patients, one would have started the study in January 1993 by including consecutively each patient who contracted an AMI or UAP, monitor the patient at regular intervals, say monthly from then on, note when the patient fulfilled the stability criteria (i.e. entered the stable state) and when the patient left the stable state again, and noting the characteristics of the new state (e.g. death). The patients included in such a design would differ from those of the CLARICOR trial in that they would include patients who entered the stable state and then died before October 1999. These patients are missing in the present PREMAC study. Thus, using the data to predict the prognosis of patients with stable CAD (as defined by the CLARICOR group), the results may very well be biased. This is the reason why we emphasise that the PREMAC study is an exploratory and hypothesis generating study.

We confined the net reclassification indices to the increase in the true-positive rate and the decrease in false-positives by including only two risk groups because when there are more than two risk categories, the indices do not adequately account for clinically important differences in shifts among risk categories [47]. We did not use category-free net classification indices because they suffer from many of the same problems as similar measures such as, e.g. the area under the receiver operating characteristic curve does. Besides, it can mislead investigators by overstating the incremental value of a biomarker, even in independent data [50].

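### Time since the qualifying AMI or UAP, which ranges from about 3 months to 7 years at entry, is not among the forced predictors, so a marker that merely tracks recency could be selected

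*SAP article*

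**What the plan says.** The SAP article's section on the patients describes a cohort "identified with a diagnosis of myocardial infarction or unstable angina pectoris during the years 1993–1999". The Discussion narrows the window to those who "contracted an AMI or UAP during the period January 1993 to August 1999". On the other end, "Exclusion criteria included AMI or UAP within the previous 3 months", and "Between October 1999 and April 2000, the 4372 patients were randomised". Follow-up for every outcome is counted from randomisation.

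The section on classification of the predictors defines the standard predictors as a complete list: clinical items, nine drug classes, hs-CRP, creatinine-based GFR and lipoproteins. The prior event enters only as "history of myocardial infarction compared to angina only, hypertension, and diabetes". The section on demographic and anamnestic data says that "history of myocardial infarction or unstable angina pectoris were obtained from the local hospital files".

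Under Flow of analyses, an advanced marker is selected if its hazard ratio differs from 1.00 at P<0.01 "when used in combination with the standard predictors", with all of those predictors forced in. The only stratification is by centre. The Discussion lists missing ventricular function, body mass index, blood pressure, medication changes, post-infarction heart failure and post-infarction angina. It does not mention elapsed time since the event.

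**The concern.** The stated aim is to find markers that improve prediction given the standard data that were available. Time since the last AMI or UAP was knowable at entry, because patients were found through diagnoses in a dated window and screened against a 3-month limit. The plan already treats recency as clinically relevant by excluding recent events. It also adds drug classes as proxies for post-infarction conditions that it could not observe.

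The background section describes several candidates as reflecting ischaemia, ventricular dysfunction, vulnerable plaque or neutrophil activation. If any of these still varies with time since the event, and risk does too, the marker takes over the omitted variable's prognostic signal. The set of selected markers is the plan's primary result. A marker selected for this reason would go on to the component outcomes, the reclassification and concordance illustrations, and the repeat analysis of the clarithromycin effect. A marker whose own relation to risk runs the other way could be masked.

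**Working it through.** The plan gives no event count or power calculation, so there is no figure of its own to reproduce.

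**1. Range of elapsed time (from the documents).**
- Longest: 1 January 1993 to 30 April 2000 is 7.3 years, or 6.8 years for someone entered on 12 October 1999, the first enrolment date.
- Shortest: the end of August 1999 to 12 October 1999 is only 1.4 months, so the 3-month exclusion sets the minimum.
- Entry therefore came about 0.25 to 7.3 years after the event.

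**2. Inputs that are assumed.** The documents give none of these:
- Elapsed time is uniform over 0.25 to 7.25 years, so SD = 7/√12 = 2.02 years.
- D = 1150 events: 55% of 2090 patients, that is, 2199 placebo patients less about 5% with a missing marker value. The plan gives 1.6 to 5.7% missing per quantity.
- The hazard falls 5, 8 or 10% per year since the event.
- The marker has no effect of its own. Its correlation r with recency is what remains after the other forced predictors.

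**3. Formula.** The log hazard ratio per SD of recency is b = −ln(1 − fall) × 2.02. This is 0.104, 0.169 and 0.213 for falls of 5, 8 and 10%, i.e. hazard ratios of 1.11, 1.18 and 1.24. Leaving recency out gives the marker an expected Z of about m = √D × r × b, and

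P(selected) = Φ(m − 2.576) + Φ(−m − 2.576).

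Example: r = 0.3 and 8% per year give m = √1150 × 0.3 × 0.1685 = 1.71, so P = Φ(−0.86) ≈ 0.19.

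| Residual r | 5%/yr | 8%/yr | 10%/yr |
|---|---|---|---|
| 0 | 1.0% | 1.0% | 1.0% |
| 0.05 | 1.1% | 1.3% | 1.5% |
| 0.1 | 1.5% | 2.3% | 3.2% |
| 0.2 | 3.1% | 7.6% | 12.9% |
| 0.3 | 6.4% | 19% | 34% |

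**4. Simulation check.**
- 1000 Cox fits per setting (2090 patients, 55% events) gave, without elapsed time, 3.0, 7.9 and 12.9% at correlation 0.2, and 6.2, 20.0 and 32.0% at 0.3. With elapsed time in the model every setting fell to 0.8 to 1.6%.
- A separate set (2199 patients, about 50% events, 400 fits per setting) gave 23% against 1.3% at r = 0.3 and a hazard ratio of 1.2 per SD. Its adjusted results ranged from 0.3 to 2.5%, which is simulation noise around 1%.

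**5. Sensitivity to the event count.** At r = 0.3 and a hazard ratio of 1.2 per SD, 40 to 60% of 2199 patients with an event gives 17 to 28%.

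**6. What the correlations imply.**
- If the marker drifts linearly, r = 0.2 or 0.3 means a change of r/√(1 − r²) × 7/2.02 = 0.71 or 1.09 residual SD over the 7 years.
- If it settles exponentially with a 1-year half-life, r = 0.2 needs a shift of about 0.96 SD at 3 months and r = 0.3 about 1.5 SD. A shift of 0.25 SD gives r of about 0.05, and 0.5 SD gives about 0.11.
- A hazard fall of 8 or 10% per year means a 44 or 52% lower hazard after 7 years (1 − 0.92⁷, 1 − 0.90⁷).

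**The case against.** The strongest reply is that this is a choice of covariates in declared hypothesis-generating, prognostic-factor work. The plan defines its standard set as specific to this study, disclaims ranking and predictive use, and nowhere says that time since the event is an established predictor. That stands against calling the omission an internal contradiction. It does not remove the point, because the plan still claims the data are useful for identifying new prognostic markers beyond what was available.

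Second, the background section says nothing about markers decaying after an event. Patients with recent events or revascularisation were excluded, and medication and hs-CRP may absorb part of any recency signal. This is fair, and it is why the small correlations in the table deserve as much weight as the large ones.

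Third, the document lists event history, not event dates, as analysis data. Screening shows that a date was knowable. It does not show that the last date was kept for every patient.

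A reader might go further than the documents allow in two ways:
- The Discussion might be read as calling enrolment at the event the right design for this study. It describes the normal design for assessing rates in stable patients, not for selecting markers.
- Delayed entry on a time-since-event scale might be thought to correct the loss of patients who died before October 1999. It cannot, because those patients have no marker values. The planned analysis already starts follow-up at randomisation, so it counts no immortal time.

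**Conclusion.** The point holds as a correctable gap in the adjustment set. Elapsed time varies from about 3 months to 7 years, it was knowable at entry, and it is neither adjusted for nor named as a limitation. Whether it matters depends on two unknowns: how steeply risk changes with time since the event, and how far each marker still tracks that time after the other forced predictors.

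Under the stated assumptions, the chance of selecting a marker with no effect of its own lies between about 1 to 4% (residual correlation 0.1 or less) and roughly 20 to 30% (correlation 0.3, hazard falling 8 to 10% per year), against the nominal 1%. Someone might take the upper figures as the plan's actual false-selection rate. The documents do not support that: they describe one demanding scenario in which risk is roughly halved over 7 years and the marker differs by about one SD. The survivor selection that the Discussion describes is a separate matter, which this change does not resolve.

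**What to change.** Add time from the last known pre-randomisation AMI or UAP to randomisation to the forced standard predictors, for the gatekeeper analysis and all component analyses. Enter it as a log term or a spline, since the return to about 1% was shown with the functional form correctly specified. Derive it from the hospital-file diagnosis dates.

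If the date is not held for every patient, keep the planned model as primary, run the extended model as a sensitivity analysis in those with a date, and list the gap among the weaknesses in the Discussion. If the date cannot be retrieved at all, that sentence in the Discussion is the minimum.

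The cost is one derived variable, 1 to 3 degrees of freedom, slightly wider intervals and a short change to the SAP text. The work of retrieving dates is uncertain until the analysis file is checked.

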### Background information on the advanced biochemical predictors

Patients with coronary artery disease (CAD) are usually only evaluated using clinical variables. But some CAD patients have a high incidence of CV insults which are difficult to predict [10]. Measurements of biomarkers may potentially help identifying CAD patients at high risk of such CV insults.

Previously, we found that increased serum N-terminal pro-B-type natriuretic peptide (NT-pro-BNP), a marker of left ventricular dysfunction, and heart failure was a stronger predictor of myocardial infarction (MI), CV death, and non-cardiovascular death than high-sensitive assay C-reactive protein (hs-CRP) in patients with CAD during a 2.6 year follow up [15]. Similar results were found for YKL-40 in the same CAD patients [16]. In this context, it is of pathogenetic interest that YKL-40 is expressed by arteriosclerotic plaque macrophages, particularly macrophages which have infiltrated into the lesion [33]. The highest expression of YKL-40 is found in macrophages in the early atherosclerotic lesion. Another promising marker is high-sensitive assay cardiac troponin T (hs-cTnT) indicating myocardial ischaemia which when combined with the NT-pro-BNP results was found to be significantly associated with all-cause mortality, CV death, and MI after adjustment for traditional risk factors and NT-pro-BNP [17]. Pregnancy-associated plasma protein-A (PAPP-A), a marker of vulnerable plaques in coronary arteries, has also been found to be predictive of CV insults and death in CAD patients [18]. The glycoprotein osteoprotegerin (OPG), which is positively related to coronary calcification, vascular stiffness, and the presence of unstable atherosclerotic plaques [34], is included among the candidate predictors because we found it to be an independent predictor of mortality in CAD patients [25]. The cathepsins are a group of proteinases that have been suggested to be causally involved in the different stages of the atherosclerotic process, from the early stages such as foam cell formation [35] to the later stages, such as destabilisation of the fibrous cap [36]. Endostatin is an endogenous angiogenesis inhibitor where circulating levels have been suggested to mirror an increased neovascularisation induced by vascular or myocardial ischaemia [37], but endostatin has also been suggested to be a marker for an increased extracellular matrix remodelling [38]. Inflammation is a key underlying factor in the atherosclerotic process [39] and tumour necrosis factor receptor alpha TNF-α, and its soluble receptors sTNFR1 and sTNFR2 are inflammatory markers that have been suggested to portray information about a systemic inflammatory state that is independent of other more established inflammatory markers such as CRP or IL-6 [40]. Previous studies report higher levels of cathepsins, endostatin, and TNF-receptors in patients with atherosclerosis and/or CAD [41–43], but whether the proteins are relevant risk markers in these patients remains to be established. Calprotectin, neutrophil gelatinase-associated lipocalin (NGAL), and myeloperoxidase are all released from neutrophils when the cells are activated. Circulating levels of neutrophils and their activation products have been shown to be markers for plaque instability in both primary and secondary prevention of cardiovascular diseases [44, 45]. We have also previously shown that U-NGAL is associated with cardiovascular mortality [23]. We now aim to explore if calprotectin is a risk marker in these patients.

### Statistical analysis

Each of the abovementioned advanced biochemical predictors will be studied individually on the below mentioned outcomes provided that the advanced quantity concerned has shown promise in the primary (‘gatekeeper’) analysis. This primary ‘gatekeeper’ analysis will examine a composite outcome, defined to be present if at least one of the events AMI, UAP, CeVD, and all-cause death has occurred in a patient. The analyses will be conducted using the Cox proportional hazard model supplemented by Breslow estimation of the baseline hazard. We will use SAS 9.4, and the analysis will be based on the data from the placebo group because it was previously shown that clarithromycin had a significant and harmful effect on the prognosis of the trial patients [10, 12–14].

#### The proportional hazards assumption

The joint proportional hazard property, covering all covariates included in a Cox analysis and the chosen functional forms of quantitative covariates, will be tested using cumulative sums of martingale-based residuals over follow-up time and/or covariate values [46]. The test statistic is a Kolmogorow-type supremum test, using for each outcome a *P* threshold = 0.05 and Bonferroni adjusted *P* values.

#### Flow of analyses

For each advanced biochemical quantity, we will examine if the hazard ratio of the biochemical quantity is different from 1.00 with a *P* value <0.01 when used alone and when used in combination with the standard predictors (forced to be included in the analyses whether they are significant or not). Using centre ID as a class variable, we will stratify on centre ID implying that the observations are conditionally independent within centres and that the coefficients of the covariates are the same across centres.

For each outcome, we will test for interaction between sex and each clinical predictor, each standard biochemical predictor, and each advanced biochemical predictor using Bonferroni adjusted *P* values and 0.05 as a threshold. The interactions corresponding to adjusted *P* values below 0.05 will be included in the model. Explanation will be sought for any marked discrepancies between the two settings (candidate used alone and candidate used in combination with standard predictors); but we will let us be guided by the results obtained when the latter setting is used.

Those advanced biochemical quantities which have a hazard ratio different from 1.00 and a *P* value <0.01 when used in combination with the standard predictors in the initial ‘gatekeeper’ analysis, will be included in subsequent and similar analyses of each individual outcome of the composite outcome.

We will use the *P* values of the analyses as a data-reducing device where a threshold of *P* < 0.01 is used at each decision node on our way to identify a candidate biochemical predictor among the advanced biochemical predictors. We regard the set of selected advanced biochemical predictors as the primary result of this essentially hypothesis-generating effort. However, clinically implausible results will be discussed and commented on.

#### Illustration of predictive impact

Nine, six and three-year estimated incident risks will be calculated for each patient using the Cox-Breslow procedure. We will illustrate discrimination by the reclassification indices, reported separately for those with and those without the event in question as recommended by Kerr et al. [47]. For example the risk estimates could be categorised as less than 25% (‘negative’) or 25% or more (‘positives’). With only two categories, this amounts to reporting the changes in the true-positive and false-positive rates.

For the mortality models, we present measures of risk differentiation, obtained by imagining preventive measures administered under budget constraints. The C statistic (Harrell’s concordance statistic) [48] represents the proportion of all patient pairs where the predicted survival is better for the patient who survived longer. The fixed budget constraint counts ‘lives saveable [by a hypothetical intervention in high-risk patients]’ [25].

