For each patient and each of the outcomes AMI, UAP, CeVD, CV death, and all-cause mortality, we scanned the discharge codes in chronological order. We began with the codes of the first admission following randomisation and recorded the period from the date of randomisation until the date of the first occurrence of the outcome or (in case of a non-fatal outcome) until the date of death or until the date of censoring (December 31, 2009) whichever came first.

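### Cox-Breslow risks of AMI, UAP and CeVD with follow-up ended at death overstate actual incidence and distort the reclassification indices; CV death is left ambiguous

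*SAP article*

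**What the plan says.** All places are in the SAP article.

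- **Vital data and diagnostic information on cardiovascular and other vascular outcomes.** Five outcomes are timed separately: "For each patient and each of the outcomes AMI, UAP, CeVD, CV death, and all-cause mortality, we scanned the discharge codes in chronological order". For a non-fatal outcome that has not occurred, the recorded period runs "until the date of death or until the date of censoring (December 31, 2009) whichever came first". The clause on death is limited to non-fatal outcomes, so it covers AMI, UAP and CeVD but not CV death.
- **Statistical analysis.** "The analyses will be conducted using the Cox proportional hazard model supplemented by Breslow estimation of the baseline hazard". The gatekeeper composite is "defined to be present if at least one of the events AMI, UAP, CeVD, and all-cause death has occurred in a patient", so every death counts as an event in it.
- **Flow of analyses.** Markers that pass the gatekeeper "will be included in subsequent and similar analyses of each individual outcome of the composite outcome".
- **Illustration of predictive impact.** "Nine, six and three-year estimated incident risks will be calculated for each patient using the Cox-Breslow procedure". Reclassification indices are then reported separately for patients who had the event and those who did not. A cut is offered as an example: "For example the risk estimates could be categorised as less than 25" per cent, against 25% or more.

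No section mentions competing risks, cumulative incidence, a subdistribution model, or combining the hazard of an outcome with the hazard of death.

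**The concern.** If follow-up for AMI ends at death and the patient enters the Cox model as censored, the fitted hazard is the cause-specific hazard of AMI. That is a sound basis for hazard ratios. Turning it alone into an absolute risk is not, because one minus the Breslow survivor function answers how many would have an AMI if nobody died of anything else first. The plan calls the result an incident risk, which it is not.

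The reclassification tables compare this predicted risk with what was observed. A patient who dies without an AMI is observed as event-free, yet the predicted risk takes no account of that death. Prediction and outcome therefore refer to different quantities. The relative overstatement is largest in patients with the highest mortality. At stake is whether the 3-, 6- and 9-year risks, and the changes in true- and false-positive rates (TPR, FPR) derived from them, mean what a reader will take them to mean.

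**Working it through.** **The plan's own figure.** The Discussion ties the 25% cut to a 3:1 cost ratio: 1/(1 + 3) = 25%. This reproduces. The plan states no event rate, so every rate below is an assumption.

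**Is 9-year status observed?** Randomisation ended in April 2000 and follow-up on 31 December 2009. From 30 April 2000 that is 9.67 years, and losses are put at 0.5%. So 9-year status is known for nearly everyone, and patients who died first are known to be without the event.

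**Formulas.** With constant cause-specific hazards λ (outcome) and δ (death without the outcome):

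- Cox-Breslow risk = 1 − exp(−λt)
- Cumulative incidence (CI) = λ/(λ + δ) × [1 − exp(−(λ + δ)t)]

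The first is never below the second, and it exceeds it whenever competing deaths occur before t. The direction is certain; only the size depends on the rates.

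**Size.** Assume a Cox-Breslow 9-year risk of 25%. Worked case with net 9-year competing death of 40%: λ = −ln(0.75)/9 = 0.0320 and δ = −ln(0.60)/9 = 0.0568, so CI = 0.0320/0.0888 × (1 − 0.75 × 0.60) = 0.360 × 0.55 = 19.8%. The ratio is 25.0/19.8 = 1.26.

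Each cell gives Cox-Breslow % / CI % (ratio):

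| Net 9-year competing death | 3 years | 6 years | 9 years |
|---|---|---|---|
| 10% | 9.1 / 9.0 (1.02) | 17.5 / 16.9 (1.03) | 25.0 / 23.8 (1.05) |
| 20% | 9.1 / 8.8 (1.04) | 17.5 / 16.3 (1.07) | 25.0 / 22.5 (1.11) |
| 30% | 9.1 / 8.6 (1.06) | 17.5 / 15.6 (1.12) | 25.0 / 21.2 (1.18) |
| 40% | 9.1 / 8.4 (1.09) | 17.5 / 14.9 (1.17) | 25.0 / 19.8 (1.26) |
| 50% | 9.1 / 8.2 (1.12) | 17.5 / 14.1 (1.24) | 25.0 / 18.3 (1.36) |

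If the Cox-Breslow 9-year risk varies from 10% to 35%, the 9-year ratio runs from 1.05 to 1.38.

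**Dependence on the death rate.** With an outcome hazard of 5% a year, the 9-year Cox-Breslow risk is 36.2% whatever the death rate. The cumulative incidence is 24.7% if death is 10% a year and 20.9% if it is 15% a year. These death rates lie outside the 10–50% range above (1 − exp(−0.9) = 59% and 1 − exp(−1.35) = 74%). They serve only to show the mechanism.

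**Effect on reclassification.** Simulation of 1,000,000 patients with a 9-year horizon and the 25% cut, comparing a model with a standard score to the same model plus a marker. Assumed log hazard ratios per SD: score 0.5 on the outcome and 0.8 on death; marker 0.3 on the outcome and 0 or 0.6 on death. The net risks in the first column are at the mean hazard.

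| Net outcome / death | Marker on death | At or above 25%: Cox-Breslow vs CI | Change in TPR / FPR, Cox-Breslow | Change in TPR / FPR, CI |
|---|---|---|---|---|
| 20% / 20% | 0 | 23.3% vs 14.3% | +0.056 / +0.011 | +0.089 / +0.031 |
| 20% / 40% | 0 | 23.4% vs 4.6% | +0.062 / +0.010 | +0.088 / +0.039 |
| 20% / 40% | 0.6 | 23.4% vs 0.0% | +0.031 / +0.015 | 0.000 / 0.000 |
| 30% / 40% | 0.6 | 53.1% vs 37.0% | −0.013 / −0.035 | +0.063 / +0.039 |

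In the second row the mean Cox-Breslow risk is 19.3% against an observed incidence of 14.6%. The Cox-Breslow change in TPR is smaller than the CI change in three rows and larger in one. In the last row both changes have opposite signs. The distortion has no fixed direction.

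**CV death.** Two readings are open. If a non-CV death is censored, the formulas above apply and the risk is overstated. If such a patient stays at risk until 31 December 2009, which is the literal reading, the risk set is of subdistribution type. Its Breslow risk is then close to a cumulative incidence, but its hazard ratio means something different from those for AMI, UAP and CeVD.

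**Composite and all-cause mortality.** Every death is an event, so δ = 0 and the ratio is 1.00.

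**The case against.** The strongest defence is that nothing decisive rests on these numbers. Flow of analyses makes the set of markers selected by Cox hazard ratio at P < 0.01 the primary result, and cause-specific hazard ratios are valid for that purpose. The section at issue is an illustration, and the Discussion says the 25% cut is not a clinical decision threshold. The Abstract advises against predictive use, and the Discussion warns that predicted prognosis may be biased by selection. All of this stands, and it limits the severity. It does not remove the point: the overstatement exists at any cut, and it would carry into the net benefit diagram that the Discussion contemplates. Nor is this detail left to a fuller document, because the article names the estimator.

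Four stronger readings are tempting and are not supported:

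- *High mortality pushes high-marker patients over the cut.* The Cox-Breslow risk contains no death hazard. The fault is that mortality fails to lower the risk.
- *The error inflates the apparent gain from a marker.* The simulations show it going either way. The change in TPR minus the change in FPR is nearly the same in two of the scenarios: 0.052 against 0.049 in the second row, and 0.022 against 0.024 in the last.
- *CV-death risks are certainly overstated.* That holds only if non-CV deaths are censored, which the plan does not say.
- *The overstatement is large throughout.* With an outcome hazard of 2% and death of 5% a year, the 9-year risks are 16.5% against 13.4% (factor 1.23), but at 3 years they are 5.8% against 5.4% (factor 1.08).

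**Conclusion.** The point holds for AMI, UAP and CeVD: as written, the 3-, 6- and 9-year risks overstate actual incidence, and the reclassification indices set them against an outcome status to which they do not correspond. The direction of the risk error is certain, on the ordinary reading that follow-up ended at death enters the Cox model as censored. Its size rests on assumed constant hazards: for a Cox-Breslow 9-year risk of 25%, a factor of about 1.05 to 1.36 at 9 years and 1.02 to 1.12 at 3 years, with net 9-year competing death of 10% to 50%. The changes in true- and false-positive rates are distorted at any cut, in a direction that the document does not determine.

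For CV death the finding is an ambiguity about how a non-CV death ends follow-up, with overstatement under one of the two readings. Marker selection, the composite and all-cause mortality are untouched. Severity is moderate.

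**What to change.** 1. Keep the cause-specific Cox hazard ratios for marker selection.
2. For AMI, UAP, CeVD and CV death, compute the 3-, 6- and 9-year risks as cumulative incidences. Combine the Cox-Breslow hazard for the outcome with that for death without the outcome, using the same covariate sets in both models and the baseline hazards of the same centre, since the plan stratifies on centre. A subdistribution (Fine-Gray) model is an acceptable alternative.
3. Use these risks in the reclassification tables and in any net benefit diagram.
4. State that in the cause-specific model for CV death follow-up ends at any death, with non-CV death modelled as the competing event. Ending follow-up at any death without the second model would itself create the overstatement.

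The cost is a few sentences in the plan and one extra cause-specific model per outcome. Vital status and cause of death are already held from the registers, so no new data are needed.
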